## Abstract

**Background:**

Disability and falls are particularly common among older people who have recently been hospitalised. There is evidence that disability severity and fall rates can be reduced by well-designed exercise interventions. However, the potential for exercise to have these benefits in older people who have spent time in hospital has not been established.

This randomised controlled trial will investigate the effects of a home-based exercise program on disability and falls among people who have had recent hospital stays. The cost-effectiveness of the exercise program from the health and community service provider's perspective will be established. In addition, predictors for adherence with the exercise program will be determined.

**Methods and design:**

Three hundred and fifty older people who have recently had hospital stays will participate in the study. Participants will have no medical contraindications to exercise and will be cognitively and physically able to complete the assessments and exercise program.

The primary outcome measures will be mobility-related disability (measured with 12 monthly questionnaires and the Short Physical Performance Battery) and falls (measured with 12 monthly calendars). Secondary measures will be tests of risk of falling, additional measures of mobility, strength and flexibility, quality of life, fall-related self efficacy, health-system and community-service contact, assistance from others, difficulty with daily tasks, physical activity levels and adverse events.

After discharge from hospital and completion of all hospital-related treatments, participants will be randomly allocated to an intervention group or usual-care control group. For the intervention group, an individualised home exercise program will be established and progressed during ten home visits from a physiotherapist. Participants will be asked to exercise at home up to 6 times per week for the 12-month study period.

**Discussion:**

The study will determine the impact of this exercise intervention on mobility-related disability and falls in older people who have been in hospital as well as cost-effectiveness and predictors of adherence to the program. Thus, the results will have direct implications for the design and implementation of interventions for this high-risk group of older people.

**Trial Registration:**

The protocol for this study is registered with the Australian New Zealand Clinical Trials Registry ACTRN12607000563460.

## Background

The development and implementation of effective strategies to minimize disability and falls among older people is an urgent public health challenge due to the increasing proportion of older people in the global population. Around 500 million people worldwide are aged 65 and older and this number is predicted to increase to 1 billion by 2030 which will represent one eighth of the global population. Developing countries are predicted to have a 140 percent increase in older people by 2030.[1]

In the World Health Organization's International Classification of Functioning, Disability and Health (ICF).[2], disability is an umbrella term for impairments (in body structure or physiological function), activity limitations (difficulties an individual may have in executing activities, tasks or actions) and participation restrictions (difficulties with involvement in life situations). Mobility is a domain of the ICF which poses difficulties for many older people. Australian data indicate that close to one quarter of people aged over 65 years report a severe or profound limitation of core activities (self-care, mobility or communication) and that 84% of these people report mobility limitations.[3] There is increasing evidence that this mobility-related disability in older people can be reduced by well-designed exercise programs. The LIFE-P randomized trial found that mobility-related disability (measured on the Short Physical Performance Scale) could be reduced with a combination of supervised and home-based exercises.[4]

At least 30% of people aged 65 and over fall at least once each year.[5] Fall rates are even higher in people who have been in hospital. Fourteen percent of people fall in the first month after discharge from hospital.[6] Systematic reviews of falls prevention strategies in older people have found that falls can be prevented by certain exercise programs.[7] In particular, ongoing exercise which targets balance can prevent up to 40% of falls.[8]

Admissions to hospital in older people are strongly associated with a decreased level of functioning and subsequent falls. A prospective study found that people without pre-existing disability are many times more likely to develop a disability within a month of a hospital stay than those who have not had hospital admission (adjusted hazard ratio = 59.8, 95% CI 46.6 to 76.8).[9] Thus, people after recent hospital stays are clearly a group who may benefit from exercise programs designed to lessen or prevent this disability. In one of the few trials of exercise in a post-hospital population [10], intensive training (three sessions a week for three months) improved physical performance significantly and between-group differences were maintained two years later.[11] We have found that home-based exercise programs which include balance and strength training can improve performance on physical tests which are predictive of falls.[12] However, it is not clear whether fall prevention exercise programs can be effectively implemented in people who have recently been hospitalized. A previous study found no effect of a seated strengthening program on fall rates in people who had been in hospital (relative risk = 0.96, 95% CI 0.67–1.36).[13]

While the increased risk of falls and disability after hospital discharge decreases with time for many individuals, for many others this risk will not return to pre-admission levels without specific intervention. Evidence suggests that a substantial number of people who have been recently hospitalized will be at an increased likelihood of falls and disability and their consequences: fractures, fear of falling, activity restriction, further decline in physical functioning and a move to institutional care.[14] Therefore, we have designed a post-hospital home-based intervention which aims to minimize disability and falls in the high-risk post-hospital population and will evaluate this intervention in a randomized controlled trial. In order for an intervention to be implemented, an understanding of its cost-effectiveness as well as its effectiveness is required. Thus, we will also conduct an economic analysis.

Adherence to exercise programs is a major issue in public health research and clinical practice. Predictors of adherence to exercise programs in older people at risk of falls and disability are not well understood [15] but useful descriptive work has been undertaken.[16] There is some evidence that longer term adherence to exercise may be better with home-based rather than center-based programs for older adults.[17] Within our randomized trial we will also establish predictors for adherence to a home-based exercise program in the post-hospital population.

To date, there is little evidence that falls and/or mobility-related disability can be minimized in older people recently discharged from hospital. This randomised controlled trial aims to evaluate the effect of an intervention primarily based on the Weight-bearing Exercise for Better Balance (WEBB) exercise program in preventing falls and minimizing disability in people who have recently been in hospital. The trial will also establish predictors of adoption and adherence to the exercise program and enable an analysis of cost effectiveness.

## Methods and design

### Design

A randomized controlled trial will be conducted among approximately 350 participants recently discharged from hospital. Figure 1 gives an overview of the study design.

**Figure 1 F1:**
[figure not shown]
**Flow of participants through the trial**.

### Participants

Participants will be consenting people aged 60 years and over who have been admitted to and subsequently discharged from participating public hospital wards in Sydney, Australia.

People will be ineligible to participate in the trial if they: reside in a high-care residential facility, have a cognitive impairment (a Folstein Mini-Mental State Examination [18] score of less than 24 after any acute confusional state has resolved), have insufficient English language skills to understand the assessment and/or intervention procedures (unless they have a carer who can assist), are unable to walk more than one meter despite assistance from a walking aid and/or another person, have a progressive neurological disease (e.g. Parkinson's disease) or suffer from any medical condition precluding exercise (e.g. unstable cardiac disease).

Interest in study participation will be sought during the hospital stay but assessment and randomization will occur after discharge from hospital and after any associated home rehabilitation organized as a result of the hospital admission.

The University of Sydney Human Research Ethics Committee (HREC) approved the study protocol (HREC Number 12-2006/9682) as have ethics committees at the participating hospitals.

### Randomization

After completion of the baseline assessment, participants will be formally entered into the study and randomized to intervention or control groups. Randomization will be stratified by hospital site and falls history (0–1 versus 2+ falls in the previous 12 months) using a computer-generated random number schedule with variable block sizes of 2–6. Randomization will be performed centrally by an investigator not involved in recruitment or assessments.

As this study involves the prescription of home-based exercise to a high risk population, safety while exercising will be a prime consideration when exercises are prescribed. Participants will be instructed how to perform exercises with stable supports (such as a table) located nearby to hold onto if needed. Where appropriate, family members and/or carers will be encouraged to assist with supervision of the exercise program. If a participant becomes unwell or has another admission to hospital, the program will be resumed when the participant and the relevant professionals deem him/her well enough to participate again.

The optimal intensity and type of exercises for each individual participant will be regularly assessed and adjusted by the study physiotherapists to ensure that the intervention remains challenging as a participant's performance improves. A manual for physiotherapists has been developed to assist in the use of this program and is available from the authors upon request.

Participants will be provided with a booklet containing safety precautions, instructions and photographs of exercises for use in exercise sessions at home. In addition, they will be provided with a logbook for recording exercises completed and effects of exercise (e.g. muscle soreness). The Physical Activity Stage of Change model [23] will be used by the study physiotherapists to guide their approach to encouraging ongoing home-based exercise participation.

The control group will receive their usual care from their medical practitioners and community services so will not be disadvantaged by being in the study.

Participants in both groups will also receive an education booklet about fall prevention.

### Outcomes

#### Data collection

Data will be collected from medical records, postal questionnaires and calendars, and physical assessments. Information on medical history, diagnoses, medication and unintentional weight loss will be collected from medical records while participants are still in hospital.

All participants will undergo three home-based assessments. The baseline assessment will be conducted prior to randomization. Further assessments will be conducted three and 12 months after randomization. Assessments will be conducted by physiotherapists or trained research assistants and will involve questionnaires and physical performance assessments. Each assessment will take about one and a half hours to complete. All assessors will be unaware of group allocation of participants they are assessing. Participants will be instructed not to inform the assessors of their intervention status, and all exercise equipment will be removed prior to assessment.

All participants will receive 12 calendars and questionnaires at the time of the baseline assessment. Participants will be asked to record falls and use of health and community services on the calendars and complete questionnaires about mobility-related disability (monthly) and quality of life (3-monthly) and return completed calendars in pre-paid envelopes to the research centre each month. Participants who do not return calendars or questionnaires will be telephoned to ask for the information. Participants who report falling will also be telephoned to seek more information about the circumstances and consequences of the fall. Staff who receive calendars and questionnaires, make follow up phone calls and enter data will be unaware of group allocation.

#### Primary outcome measures

Mobility-related disability and falls are the primary outcome measures in this trial.

Mobility-related disability will be measured monthly with a self-reported test and at 3- and 12-months after randomization using a performance-based test. The monthly mobility measure will involve a self-reported questionnaire about difficulty in mobility tasks using the physical and movement items suggested by Haley et al.[24]

The performance-based mobility measure will be the lower extremity Summary Performance Score version [25] of the Short Physical Performance Battery.[26] This battery gives a composite score based on timed performance of three mobility tasks: the ability to stand for up to 10 sec with feet in different positions (together side by side, semi-tandem and tandem), 4-meter walk and time to rise from a chair five times.

Falls will be measured monthly using the calendars as outlined above. A fall will be defined according to the Kellogg definition [27] as an incident in which the body unintentionally comes to rest on the ground or other lower level which is not as a result of a violent blow, loss of consciousness, sudden onset of paralysis as in a stroke or an epileptic seizure.

#### Secondary outcome measures

Secondary outcome measures will be risk of falling, additional measures of mobility, strength and flexibility, quality of life, fall-related self efficacy, health-system and community-service contact, assistance from others, difficulty with daily tasks, physical activity levels and adverse events. These aim to enhance understanding of the effects of exercise on multiple factors that contribute to an older person's abilities and quality of life, and to enable economic analyses to be conducted. These outcome measures are described below.

Fall risk will be assessed using the *Physiological Profile Assessment *[28] which includes measures of knee extension strength, postural sway, lower limb proprioception, reaction time and visual contrast sensitivity. *Choice Stepping Reaction Time *has been found to be a composite measure of risk of falling when assessed with an electronic device.[29] We will measure this in a modified manner with a portable mat. A mat with four white squares will be placed in front of the standing subjects, and they will be asked to make a standard number of steps with either foot to a particular square and back again, using a standardized script. The time for the entire routine will be recorded in seconds.

Additional measures of mobility to further explore posited effects of the intervention will be assessed using the *Maximal Balance Range *and *Coordinated Stability Tests*.[30] The Maximal Balance Range test assesses subjects' ability to lean as far forward and backwards as possible. The Coordinated Stability requires subjects to adjust their body position in a steady and coordinated manner when near the limits of their base of support. *Grip strength *will be assessed using a portable dynamometer (JAMAR Hydraulic Hand Dynamometer manufactured by Sammons Prestons). *Ankle flexibility *will be measured in a torque-controlled manner using a modification of the Lidcombe template procedure [31] in which the person is sitting rather than lying and an inclinometer is used to assess changes in ankle angle. In addition, the effects of the intervention on the individual components of the Short Physical Performance Battery and single leg stance time will be assessed.

Quality of life will be assessed using the *SF 12*™*Version 2 *at baseline, 3 and 12 months and each 3 months using the postal *EQ-5D*.[32]

Fall-related self-efficacy will be assessed using the *Falls Efficacy Scale-International *[33] in which level of concern about falling when carrying out a range of activities is rated on a 4-point scale.

*Health and community service contact *will be assessed using calendars as described above. Participants will be asked about the need for *assistance from others*.

*The level of difficulty with daily tasks *will be assessed using the personal care and instrumental items suggested by Haley at al.[24]

*Physical activity levels *will be assessed with the Physical Activity Questionnaire for older people (developed by [name]).

Exercise *program adherence rates *and *minor adverse effects *(eg. muscle pain not limiting daily activities) of the exercise program will be monitored using exercise diaries kept by participants. Participants will be advised to telephone study staff if they experience any *major adverse effects *(e.g. chest pain, muscle soreness lasting for more than 48 hours and interfering with daily activities or requiring medical attention).

*Exercise self-efficacy *will also be assessed and participants will be asked to *identify reasons for exercise adherence *at the follow-up interviews.

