### Statistical analysis

The number of falls per person-year will be analyzed using negative binomial regression to estimate the difference in fall rates between the two groups.[34] The proportion of fallers in the two groups will also be compared using the relative risk statistic. Longitudinal mixed models will be used to assess the effect of group allocation on the continuously-scored primary and secondary outcome measures. Logistic regression models will be used to compare groups on dichotomous outcome measures. An intention-to-treat approach will be used for all analyses. Analyses will be conducted using the SPSS and STATA software packages. Predictors of exercise adherence will be established using multivariate modeling techniques.

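### Adverse events are a trial-wide secondary outcome, but symptoms that lead to neither a fall nor service contact have no parallel capture in the control group

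*Protocol article*

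**What the plan says.** In the protocol article, the opening paragraph of Secondary outcome measures ends its list with "assistance from others, difficulty with daily tasks, physical activity levels and adverse events". It names no arm and says that the measures are described in what follows.

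The description comes later in the same section and has two routes:

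- **Minor adverse effects** share a sentence with adherence rates. Both are "of the exercise program will be monitored using exercise diaries kept by participants".
- **Major adverse effects** depend on self-report: "Participants will be advised to telephone study staff if they experience any" of them. The examples are chest pain and prolonged muscle soreness that interferes with daily activities or needs medical attention.

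The Intervention section shows who holds the recording instrument. After the exercise booklet, it says of those taking part in the program that "they will be provided with a logbook for recording exercises completed and effects of exercise". It then says: "The control group will receive their usual care from their medical practitioners and community services". The only item that this section gives to both groups is an education booklet on fall prevention.

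The Statistical analysis section states: "Logistic regression models will be used to compare groups on dichotomous outcome measures". It applies intention-to-treat to all analyses and makes no exception for adverse events.

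**The concern.** The outcome is named as events occurring in the trial but measured as effects of a program that controls do not receive. Someone in the exercise arm with a sore knee has a logbook that asks about it and a physiotherapist who visits ten times in the year. A control participant with the same knee has neither.

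Two uses of the data are possible, and each has a problem. If the arms are compared, part or all of any excess in the exercise arm may reflect who was asked. If they are not compared, the trial has a list of symptoms in exercisers and no background rate to set against it. Participants are aged 60 and over and recently out of hospital, so pain and similar complaints can be expected without any exercise program. The article aims at a program that could be widely implemented, so a spurious excess of symptoms, or an uninterpretable list of them, would matter to those deciding on its use.

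**Working it through.** The article gives no figure to reproduce. The check is to trace each kind of harm to its source in each arm, then to see what unequal capture does to a comparison.

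**Step 1. Capture by arm, as described in the protocol article**

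| Harm | Intervention | Control | Where described |
|---|---|---|---|
| Falls | Monthly calendar | Monthly calendar | Data collection; Primary outcome measures |
| Circumstances and consequences of falls | Telephone follow-up | Telephone follow-up | Data collection |
| Health and community service use, including admissions and emergency presentations | Calendar | Calendar | Data collection; Economic analysis |
| Minor adverse effects | Exercise diary | None described | Intervention; Secondary outcome measures |
| Major adverse effects | Self-initiated call | Unclear whether advised to call | Secondary outcome measures |

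The first three rows are symmetric, and the staff who handle calendars and follow-up calls are unaware of allocation. The fourth row is one-armed as described. The fifth is ambiguous. Its sentence refers to participants without naming an arm, but the sentence before it and the soreness example point to exercisers. If controls are advised too, the route is still passive, while only exercisers have a logbook and visits to prompt them.

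**Step 2. What remains uncovered**

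An event that leads to a fall or to service contact should leave a record in both arms, though not one labelled as an adverse event. What lacks parallel capture is pain, soreness, chest symptoms and similar events that the participant manages alone.

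**Step 3. Effect on a comparison**

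Let p be the true 12-month risk, equal in both arms, and let c1 and c0 be the probabilities that an event is recorded in the intervention and control arms. Then:

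observed risk ratio = (p × c1) / (p × c0) = c1 / c0

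The true risk cancels. The article gives no capture probabilities, so the values below are assumptions shown over a range:

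- c1 = 0.80, c0 = 0.20: 0.80 / 0.20 = 4.0
- c1 = 0.80, c0 = 0.40: 0.80 / 0.40 = 2.0
- c1 = 0.80, c0 = 0.60: 0.80 / 0.60 = 1.3

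To put this in participants, assume also p = 0.20, with the planned 175 per group. The intervention arm would show 0.20 × 0.80 × 175 = 28. The control arm would show 0.20 × 0.20 × 175 = 7, 0.20 × 0.40 × 175 = 14 or 0.20 × 0.60 × 175 = 21. In none of these cases has exercise caused any harm.

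**The case against.** The best case on the other side has five parts.

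1. **No adverse-event comparison is specified.** The Statistical analysis section does not name adverse events or say that they are dichotomised. Minor effects share a sentence with adherence, which is plainly an intervention-arm measure, so descriptive monitoring may be all that is meant. This stands in part: the article does not commit itself to a biased test. But it lists adverse events as a secondary outcome without restriction and exempts them from nothing, and descriptive use still leaves no background rate.

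2. **Controls may in fact be asked.** The telephone advice may cover both arms, the content of the home-assessment questionnaires is not itemised, and a journal article condenses. This stands as a limit on certainty. The point does not rest on silence, however. The article states a method for this outcome, and the diary part of it is one-armed.

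3. **Important harms are captured equally.** This stands. A reader might infer that the trial cannot show whether the program is safe, but the document does not support that. Falls are a primary outcome collected monthly in both arms, their consequences are followed up in both, and so is service use.

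4. **The numbers are assumptions.** This also stands. The ratio of 4.0 is the assumed 80/20 capture ratio and nothing more. The calculation also uses one capture rate per arm for minor and major events, although their routes differ, and it supposes that exercisers log background symptoms although the logbook is framed around effects of exercise. A reader should not take a fourfold excess as a forecast.

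5. **The bias is conservative.** In a comparison it would run against exercise and could not make the program look falsely safe, and no primary outcome is affected. This limits the severity but does not make the comparison valid.

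**Conclusion.** The point holds for a defined part of the safety data. As described, adverse events that lead to neither a fall nor service contact are sought in exercisers through a diary and have no matching enquiry in controls. They cannot be compared fairly between arms, and without a comparison they cannot be attributed to the program. The direction of bias, against exercise, needs only that prompted capture exceeds unprompted capture. Its size depends on capture probabilities that the article does not give; over the assumed range the spurious risk ratio is 1.3 to 4.0.

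The conclusion rests on reading the diary as an intervention-arm instrument, which the Intervention section supports, and on there being no symptom enquiry in the assessments common to both arms, which the article does not settle. The primary outcomes, the sample size and the two-arm comparisons of falls and service use are untouched. This is an inexpensive improvement that should be made, not a flaw that undermines the trial.

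**What to change.** Add two or three identical items to the monthly calendar for both arms, for example new pain or injury limiting activity, and symptoms needing medical attention. They should ask whether the event occurred, not whether exercise caused it, so that controls can answer on the same terms. The existing arrangements then apply: all participants receive calendars, non-returns are followed up by telephone, and the receiving staff are unaware of allocation.

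State that the between-group adverse-event comparison uses these items together with falls and service use. State that diary and telephone events are reported descriptively for the intervention arm only, and say whether controls are also advised to telephone.

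The cost is a calendar reprint, a data-entry field and a small added burden for participants. If the calendar cannot be changed, the statement on descriptive reporting is the minimum. It removes the biased comparison but leaves background symptoms unmeasured.
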